## Withdrawal of subjects

A subject may voluntarily withdraw or be withdrawn from the study at any time for reasons including, but not limited to, the following:

- The subject wishes to withdraw from further participation.
- Continuation in the study would be impracticable or detrimental to the subject’s safety in the opinion of the Investigator.

If a subject is discontinued prematurely from the study, the investigator must provide an explanation in writing and complete the appropriate study discontinuation assessments. If study drug has been administered, the investigator should make every effort to perform all scheduled evaluations, unless the subject has withdrawn consent for study participation.

In the event a subject discontinues treatment prematurely due to an AE, the AE will be followed until it resolves (returns to normal or pretreatment values) or stabilizes, or until it is judged by the investigator to be no longer clinically significant.

Subjects who discontinue participation in the study prior to receiving study drug will be replaced by randomizing an additional subject. Subjects who discontinue participation after receiving study drug will not be replaced.

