# study design

## Overall study design and flow chart

The study is a single-blinded, sequential design, single centre pilot study in HIV-positive subjects on treatment (ART). Twenty-four subjects will be enrolled into one of four treatment groups.

| **Group** | **Treatment** | **No. of subjects in Europe** |
| --- | --- | --- |
| 1 | 80 µg Vacc-4x + Endocine* | 6 |
| 2 | 400 µg Vacc-4x + Endocine* | 6 |
| 3 | 1.2 mg Vacc-4x + Endocine* | 6 |
| 4 | Endocine* | 6 |

* adjuvant

Subjects who have been HIV-positive and stable on ART for the last 6 months and CD4 cell counts ≥400x 10 6 /L and who meet the other inclusion and exclusion criteria will be eligible for the study. The duration of the main study is 8 weeks plus a screening period of up to 4 weeks. A study flow chart is presented in Table 2.

Table 2 Study Flow Chart

| **PARAMETERS** | **Weeks**  **Day** | **-4** | **1 2 3 4**  **1 8 15 22** | | | | | **8 END**  **50-53 (DTH)** | | |
| --- | --- | --- | --- | --- | --- | --- | --- | --- | --- | --- |
| Visits | 1 | 2 3 4 5 | | | | |  | | |
|  | Scree-ning | Immunization  period | | | | | | Follow-up  period | |
| Randomization | | x |  |  |  |  |  |  | |  |
| Immunizationa)  VACC-4x / Endocine | |  | x | x | x | x |  |  | |  |
| DTH-test b) | |  |  |  |  |  |  |  | | x |
| Adverse event | |  | x | x | x | x |  |  | | x |
| Vital signs/Physical examinationc) | | x | x |  |  | x |  |  | | x |
| Blood sample:  general safety d) | | x | x |  |  | x |  |  | | x |
| Blood sample:  Viral load (HIV-1 RNA), CD4 | | x | x |  |  | x |  |  | | x |
| Blood sample:  T-cell responsee) | | X | X | x | x | X |  |  | | X |
| Sampling of mucosal secretions | |  | x |  |  | x |  |  | | x |
| Urine sample | |  | x |  |  |  |  |  | | x |
| Inclusion/Exclusion | | x |  |  |  |  |  |  | |  |
| Informed consent | | x |  |  |  |  |  |  | |  |

1. 150µl to be administered in each nostril
2. DTH skin reaction; to be registered at 48 hours after immunization.
3. Body weight, height (at baseline only), blood pressure, heart rate, concomitant disease, concomitant medication
4. Hb, CRP, WBC (incl. diff), Platelets, Creatinine, Na, K, AST, ALT, LDH, ALP, -GT, Albumin, Total Bilirubin, Beta2-microglobulin. In addition, the subjects HLA type can be registered.

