## Procedures by main study phases

### Pre-treatment period

#### Screening visit (Visit 1) (Week -1 to –4)

Having given consent, subjects will undergo screening assessments to determine whether they are eligible to participate in the study according to the criteria listed in Section 5.2 and Section 5.3. The following evaluations will be performed during screening:

- Review of inclusion/exclusion criteria
- Medical/surgical history (including current disease, pre‑ART CD4 counts, and pre‑ART HIV-1 viral load)
- Physical examination (including height)
- Vital signs (blood pressure, heart rate)
- Clinical chemistry and hematology (hemoglobin, CRP, WBC, platelets, creatinine, Na, K, AST, ALT, LDH, ALP, -GT, albumin, total bilirubin, 2-microglobulin).
- Viral load (HIV-1 RNA) andCD4 counts
- T cell responses.
- Concomitant medications and AEs

At the investigator’s discretion, laboratory tests may be ordered through the local laboratory to confirm a subject’s current status regarding chronic active infections or AIDS related illnesses in order to confirm eligibility in the trial if the status is not sufficiently documented in the subject’s medical records.

***Randomization:*** When the results of the screening evaluations are available to confirm eligibility the subjects will be randomized.

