#### Visit 2 (Week 1 - Day 1)

This visit will occur at least five days but not more than 28 days after the screening visit. The following procedures will be performed in the following order (it is important that all blood samples are taken before drug administration):

- Review of concomitant medications and AEs
- Physical examination, including weight
- Vital signs
- Clinical chemistry and hematology and optional HLA type
- Viral load (HIV-1 RNA) and CD4 counts
- T-cell responses
- Collection of mucosal sections
- Collection of urine
- Administration of study drugs via intranasal administration

The subject should remain in the clinic for 30 min after the administration of study drug to be monitored for adverse reactions to the immunization.

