## Determination of sample size

It is decided that 6 subjects should be included in each of the four study arms. As this is a pilot study, the sample size has primarily been determined to provide descriptive statistics for the safety and efficacy parameters.

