## Populations to be analyzed

The following populations will be used in the analysis:

Intention to treat (ITT): Consistent with the intent-to-treat principle, all subjects receiving treatment will be included in the safety and efficacy analyses (full analysis population as defined by ICH-E9).

Per protocol (PP): All ITT subjects who receive the full immunization and who do not incur any major protocol violations that would challenge the validity of their data will be included in an additional analysis of main the efficacy parameters.

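### Randomising at screening leaves up to 28 days before dose 1 in which a subject can drop out of the treated-only ITT set and be replaced, with neither concealment nor the replacement's arm stated

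*Protocol*

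**What the plan says.** **Time of randomisation.** Section 7.3.1 (Screening visit): "When the results of the screening evaluations are available to confirm eligibility the subjects will be randomized". The flow chart (Section 4.1, Table 2) marks randomisation in the screening column only.

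**Time of dose 1.** Section 7.3.2, on Visit 2: "This visit will occur at least five days but not more than 28 days after the screening visit". Before dosing, that visit repeats the review of adverse events and medication, the examination and the blood samples.

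**Loss and replacement.** Section 5.4 lets the subject leave at any time, and lets the investigator withdraw a subject whose continuation is judged unworkable or harmful. The rule for those not yet dosed is: "Subjects who discontinue participation in the study prior to receiving study drug will be replaced by randomizing an additional subject". For the others: "Subjects who discontinue participation after receiving study drug will not be replaced".

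**Analysis set.** Section 11.3 invokes the intention-to-treat principle but defines the set by treatment: "all subjects receiving treatment will be included in the safety and efficacy analyses".

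**Planned numbers.** Section 4.1: "Twenty-four subjects will be enrolled into one of four treatment groups". Section 11.1: "It is decided that 6 subjects should be included in each of the four study arms". The same section explains that "the sample size has primarily been determined to provide descriptive statistics for the safety and efficacy parameters". Section 4.1 also opens the study with a stage of five subjects, two on adjuvant alone and three on the lowest dose, before the next dose level starts.

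**Blinding and allocation.** The study is called single-blind. Section 11.2 names the software used to randomise, and Section 6.4 lists the groups. Neither says who is blinded, how the arm is concealed until dosing, or which arm a replacement receives.

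**The concern.** Leaving randomised but undosed subjects out of the analysis is harmless when the decision not to dose cannot depend on the arm. This plan gives no such assurance. Allocation is made before it is needed, withdrawal is partly discretionary, Visit 2 offers several occasions for it before dosing, and a single-blind design leaves open that site staff know the arm. If a withdrawal were influenced by the arm, the treated groups would no longer be the groups that randomisation formed. Section 11.6.3 plans ANCOVA and Cochran-Mantel-Haenszel comparisons between arms, with adjuvant alone as the reference, and these rely on that comparability. A statistical analysis plan written later cannot repair a selective loss; only trial conduct can prevent it.

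The second matter is balance. Replacement is evidently meant to keep six dosed subjects per arm, but the wording does not tie the new subject to the arm or the stage of the one who left.

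**Working it through.** **Planned size.** 4 arms × 6 subjects = 24, which agrees with the stated total. There is no power calculation to reproduce.

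**Length of the gap.** Visit 2 is 5 to 28 days after the screening visit. Randomisation waits for the screening results, so it falls after that visit. The time from randomisation to dose 1 is therefore at most 28 days and usually less.

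**Where an undosed subject appears.** The treated-only set excludes the subject, and the per-protocol set is a subset of it. The disposition summary in Section 11.5 covers everyone randomised, so the loss is reported there but not analysed.

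**How often this could arise.** The Protocol gives no pre-dose loss rate. Assuming a rate d, independent across 24 subjects, the chance of at least one loss is 1 − (1 − d)^24:

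| Assumed d | Chance of at least one loss |
| --- | --- |
| 2% | 38% |
| 5% | 71% |
| 10% | 92% |

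**Whether six per arm survives.** This depends on a rule that the Protocol does not state, so both cases are shown.

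*Case A: the replacement takes the vacated place.* Treated numbers stay 6/6/6/6 for any number k of losses, and 24 + k subjects are randomised.

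*Case B: each replacement is an independent, unrestricted 1:1:1:1 draw.*
- One loss: the chance that the draw returns the same arm is 1/4 = 25%.
- Two losses from different arms: 2 × (1/4)² = 12.5%. Two from the same arm: (1/4)² = 6.25%.
- Two losses taken at random from 24: the second shares the first one's arm with chance 5/23, so 18/23 × 12.5% + 5/23 × 6.25% = 11.1%.
- Three and four losses at random, by the same reasoning: 6.6% and 4.5%.

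*Case B in the opening stage.* Only two groups are open, at 2:3, so the four-arm figures do not apply. A fresh 2:3 draw returns the same arm with chance 2/5 = 40% if an adjuvant subject is lost and 3/5 = 60% if a low-dose subject is lost.

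**What an imbalance costs.** With equal variances, the standard error of a two-arm difference is proportional to √(1/n₁ + 1/n₂).

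| n₁ v n₂ | √(1/n₁ + 1/n₂) | Relative to 6 v 6 |
| --- | --- | --- |
| 6 v 6 | 0.5774 | 1.000 |
| 5 v 7 | 0.5855 | 1.014 |
| 5 v 6 | 0.6055 | 1.049 |

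For safety, the exact two-sided 95% upper limit when no event is seen is 1 − 0.025^(1/n): 45.9% for n = 6 and 52.2% for n = 5.

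**The case against.** A fair defence makes five points.

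- **The replacement's arm is unstated, not stated wrongly.** A list that closes each arm at six would send the replacement to the vacated place, and list construction is often left to a separate randomisation plan. This stands. A reader might infer that the rule breaks six per arm and leaves groups of five and seven; the text does not support that. The 25%, 12.5% and 6.25% figures need an unrestricted four-arm draw, which the Protocol nowhere specifies and which does not fit the staged opening.
- **Arm-related selection is not shown.** A reader might also infer that staff will choose whom to dose knowing the arm. No section says that the investigator knows the arm before dose 1, and Section 6.3.3 gives preparation to the pharmacist or another responsible person. This stands, so the point is only that nothing excludes selection.
- **Restoring the subject to the analysis would change little.** Missing data are not imputed (Section 11.4), and a subject without a post-baseline value is left out of change-from-baseline analyses (Section 11.6). A treated set also suits the primary objective, which is safety. This stands, and it is why the remedy lies in the time of randomisation rather than in re-including undosed subjects.
- **Losses are visible.** Disposition covers all randomised subjects, and Section 5.4 asks for a written explanation of premature discontinuation. True, but a listing by assigned arm is not specified.
- **The trial is a small descriptive pilot.** This limits the size of the point. It does not remove it, because between-arm tests are planned and the gap is avoidable.

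**Conclusion.** The point holds as a limited one. The Protocol places randomisation up to 28 days before dosing, permits discretionary withdrawal in between, removes the undosed subject from a set it calls intention-to-treat, and replaces that subject by randomising another. With no statement of who is blinded or how the arm is concealed, this may allow arm-related selection, and it does not secure six per arm or the two-to-three opening split.

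The loss of precision is small: about 1.4% in the standard error for five against seven, and 4.9% for five against six. Any selection bias cannot be sized from the document. How often the situation would arise rests on the assumed loss rates, and the chance of imbalance rests on how replacements are drawn, which is not stated. The change is worth making before enrolment because the gap has no evident purpose and is easily closed.

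**What to change.** 1. In Section 7.3, place randomisation at Visit 2, after the pre-dose review and samples and immediately before the dose is prepared. Move the entry in Table 2 from the screening column to the Visit 2 column. This removes almost all of the interval in which a post-randomisation, pre-dose loss can occur.
2. In Section 5.4, state that if a randomised subject is still not dosed, the replacement is assigned to the same stage and arm through the pharmacy, with the allocation concealed from the staff who enrol and assess subjects. Treated numbers then stay at 6/6/6/6.
3. In Section 11.3, call the treated-only set a modified intention-to-treat (treated) set.
4. In Section 11.5, list undosed subjects by assigned arm.

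**Cost.** These are changes of wording in the Protocol and the flow chart. Allocation must be handled on the dosing day. The extra work should be small, since Sections 6.1.1 and 6.3.3 already have the formulation mixed around the time of administration. The real drawback is that a vacated place is predictable to anyone who knows the lost subject's arm, so step 2 is safe only if the concealment is kept. Replacement in the same place restores balance but does not by itself prevent selection; step 1 is what addresses that.

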### Vaccine toxicity management

#### Administration site reactions

The following local reactions will be reported:

- Pain, tenderness, acute swelling or soreness at the application site (nose). The severity of pain or other reactions will be categorized as: None,’ ‘Mild’ (awareness of symptom but easily tolerated), ‘Moderate’ (discomfort enough to cause interference with usual activities), or ‘Severe’ (incapacitating with inability to work or do usual activity)

For administration site reactions judged to be life-threatening or severe, the investigational drug substance suppliers should be notified within 24 hours, and further vaccines should not be given to the subject prior to consultation with the suppliers.

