## Potential Risks and Benefits

Participants will provide important scientific information that may contribute to improved management of future HIV-positive subjects. Potential benefits for participants include a possible sustained improvement in the immune response to p24 and HIV. All patients will continue their regular ART regimen throughout the study and the study design does not involve scheduled ART interruption. Potential risks include the discomfort and inconvenience associated with the immunizations and the risk of known or unknown side effects of exposure to Vacc-4x given as intranasal administration with Endocine as adjuvant.

After intranasal administration the most common types of adverse events are expected to be related to local irritation of the nasal mucosa.

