# Study objectives AND ENDPOINTS

## Study objectives

### Primary objective

The primary objective of this study is to evaluate the safety of intranasal administration of Vacc-4x with Endocine as adjuvant at three different dose levels.

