### Follow‑up period

The follow-up period consists of a 4-week period following the Week 4 visit.

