### Vital signs

At screening, week 1, week 4 and week 8 (end of study) vital signs (heart rate, systolic and diastolic blood pressure) will be measured prior to administration of study drug (if applicable) with the subject in the sitting position. Vital signs will be measured after the subject has been sitting at rest for 5 minutes.

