# Adverse Event Management

## Non‑serious and serious adverse events

The investigator is responsible for the detection and documentation of events meeting the criteria and definition of an AE or SAE as provided in this protocol (see below). All AEs and SAEs that occur from the time written informed consent is obtained until completion of the study, week 8, will be entered on the appropriate CRF page (see Section 9.1.4). Information to be collected includes the description, date and time of onset, intensity, duration, causality, and outcome of the event. Even if the AE is assessed by the investigator as not reasonably attributable to study drug, its occurrence must be recorded in the source documents and reported on the CRF.

Periodically during the study, after the subject has had an opportunity to spontaneously mention any problems, the investigator should inquire about the occurrence of AEs. The following are examples of open‑ended questions that may be used to obtain this information:

- “How are you feeling?”
- “Have you had any medical problems since your last visit/assessment?”
- “Have you taken any new medicines, other than those given to you in this study, since your last visit/assessment?”

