## Study monitoring and auditing

In accordance with applicable regulations, GCP, and the procedures of the investigational drug substance suppliers (or designee), the study monitor will periodically contact the site and conduct on‑site visits. The extent, nature, and frequency of on‑site visits will be based on study complexity, enrollment rate, and data quality at the site. Through frequent communications (e.g., letter, e‑mail, telephone), the study monitor will ensure that the investigation is conducted according to protocol and regulatory requirements.

During these contacts, the monitoring activities will include:

- Checking and assessing the progress of the study.
- Reviewing study data collected to date for completeness and accuracy.
- Conducting source document verification by reviewing each subject’s CRF against source documents (e.g., medical records, subject diaries, ICF, laboratory result reports, raw data collection forms).
- Identifying any issues and addressing resolutions.

These activities will be done in order to verify that the:

- Data are authentic, accurate, and complete.
- Safety and rights of the subjects are being protected.
- Study is conducted in accordance with the currently approved protocol (and any amendments), GCP, and all applicable regulatory requirements.

The investigator will allow the study monitor direct access to all relevant documents, and allocate his/her time and the time of his/her staff to the study monitor to discuss findings and any relevant issues.

In addition to contacts during the study, the study monitor will contact the site prior to the start of the study to discuss the protocol and data collection procedures with site personnel.

At study closure, study monitors will conduct all activities as indicated in Section 12.9.

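### The named local reactions include no specifically nasal symptom, and mild nasal irritation is left to open questions 7 days after doses 1 to 3 and about 28 days after dose 4, so it may be under-recorded for the primary safety objective

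*Protocol*

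**What the plan says.** Section 3.1.1 sets the aim: "The primary objective of this study is to evaluate the safety of intranasal administration of Vacc-4x with Endocine as adjuvant at three different dose levels". Section 2.7 says that "the most common types of adverse events are expected to be related to local irritation of the nasal mucosa".

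Section 5.4.1 names the local reactions to report: "Pain, tenderness, acute swelling or soreness at the application site (nose"). It grades them from none to severe, and the grading sentence extends to reactions other than pain.

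Section 9.1 sets how AEs are found. After the subject has had a chance to mention problems unprompted, "the investigator should inquire about the occurrence of AEs", with general questions given as examples. All AEs from consent to week 8 must be entered. Section 9.1.4 requires any new or worsening condition after dosing to be recorded, and section 3.2.1 covers scheduled and unscheduled visits.

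The visit lists in section 7.3.2 put AE review first and dosing later, and end each dosing visit with a 30-minute stay. Section 7.3.3 says that follow-up "consists of a 4-week period following the Week 4 visit". Neither Table 2 nor any visit list contains a nasal symptom checklist, a diary or a post-dose contact.

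**The concern.** For a study of whether the nasal route is tolerable, the expected local signal is irritation that is often mild and brief. The four named terms would not prompt a subject to report discharge, blockage, sneezing, itching, burning, bleeding or a change in smell or taste. The duty to record all AEs covers only what is volunteered or elicited, and the questions are general.

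The severity scale in section 5.4.1 has a none category. It can be completed only if someone asks about local reactions, yet no visit lists that assessment. Section 9.1.4 also asks for a diagnosis in place of a cluster of symptoms, so a runny nose with congestion and sneezing could be entered as a cold.

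The AE summaries in section 11.6.2 are the main output for the primary objective. With 6 subjects per arm and a descriptive design (section 11.1), one or two missed subjects visibly change an arm's result. A statistical analysis plan cannot repair this, because a symptom that nobody asked about leaves no data to analyse.

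**Working it through.** **Recall gaps.** Doses are on Days 1, 8, 15 and 22, and the AE review after the last dose is on Day 50 (section 7.3). AE review precedes dosing, so the next scheduled review of each dose is at the following visit:

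- Dose 1: 8 − 1 = 7 days
- Dose 2: 15 − 8 = 7 days
- Dose 3: 22 − 15 = 7 days
- Dose 4: 50 − 22 = 28 days, which reproduces the stated 4-week follow-up

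If the visit windows of 1 day (Days 8, 15 and 22) and 3 days (Day 50) are read as plus or minus, the gaps are 6–8, 5–9, 5–9 and 24–32 days.

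**Share of dosing affected by the long gap.** 4 arms × 6 subjects = 24 subjects; 24 × 4 doses = 96 administrations; dose 4 is 24/96 = 25%.

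**Effect on the comparison with Endocine alone.** Let p₁ and p₀ be the true proportions with irritation on vaccine and on adjuvant alone, and c the proportion captured, the same in every arm. The recorded difference is c·p₁ − c·p₀ = c(p₁ − p₀), smaller than the truth when c < 1. The recorded ratio, c·p₁ / c·p₀, is unchanged.

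**What incomplete capture could do.** The Protocol gives neither a reaction rate nor a capture rate, so everything from here on is assumed.

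Chance of recording at least one affected subject in an arm of 6, 1 − (1 − p·c)⁶:

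| True rate p | c = 100% | 75% | 50% | 25% |
| --- | --- | --- | --- | --- |
| 20% | 74% | 62% | 47% | 27% |
| 40% | 95% | 88% | 74% | 47% |
| 60% | 99.6% | 97% | 88% | 62% |

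**What the 28-day gap alone could do.** Suppose doses 1 to 3 are fully captured, reactions are independent between doses with probability q each, and a fraction c₄ of dose-4 reactions is captured. The share of subjects with any recorded reaction is 1 − (1 − q)³(1 − q·c₄):

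| Per-dose rate q | c₄ = 1 | c₄ = 0.5 | c₄ = 0 |
| --- | --- | --- | --- |
| 10% | 34% | 31% | 27% |
| 20% | 59% | 54% | 49% |
| 40% | 87% | 83% | 78% |

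Under these assumptions the long gap on its own costs 3 to 10 percentage points. Larger losses need poor capture after the other doses too, which depends on how the question is asked.

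**The case against.** The best case for the plan is that nothing is excluded. The grading sentence in section 5.4.1 reaches beyond pain, and sections 9.1 and 9.1.4 make any new nasal symptom reportable, listed or not. Acute swelling and soreness may cover some congestion and irritation. Each dose is followed by at least 30 minutes of observation, three of the four doses are reviewed within about a week, and unscheduled visits count. The two-week safety evaluation before the next dose level (section 4.1) rests on the 7-day gaps, not the 28-day one. Collection is the same in all arms, so equal under-recall does not by itself distort the ratio between them.

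All of this stands, and it narrows the point to prompting and timing. It does not remove it: a duty to record does not make a subject mention a blocked nose that cleared days ago, and 30 minutes catches only immediate reactions.

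A reader might infer more in three ways, none of them supported:

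- **That the list limits reporting, or was carried over from an injection protocol.** The text says application site (nose). Visit 4 does still refer to intradermal injection, so carry-over is plausible, but it is not shown for this list.
- **That a diary was planned and forgotten.** Section 12.7 mentions "medical records, subject diaries, ICF, laboratory result reports, raw data collection forms" as examples of source documents in general monitoring text, not as a study procedure.
- **That vital signs taken only before dosing add to the problem.** Heart rate and blood pressure say nothing about nasal irritation.

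**Conclusion.** The point holds as a weakness in data collection for the primary objective. The reaction type expected most often has no specific prompt, and recall runs to 7 days after three doses and about 28 days after the fourth (25% of administrations). Mild, transient irritation may be under-recorded in every arm, lowering absolute incidence and narrowing absolute differences from Endocine alone.

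The documents do not show that it will be under-recorded, or by how much. The day counts follow from the Protocol; every capture figure above is conditional on assumed rates. The statement about differences assumes equal capture across arms. It would also be wrong to treat the 28-day gap as typical, since it applies to one dose in four.

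**What to change.** Keep the four terms in section 5.4.1 and add nasal symptoms: blocked or runny nose, sneezing, itching or burning, bleeding, and altered smell or taste. Collect the whole list as a fixed, solicited checklist at three kinds of existing contact:

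- the AE review before each dose (at Visit 2 this also gives a pre-treatment baseline);
- the end of the 30-minute stay;
- Visit 6.

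Add a one-page 7-day diary card after each dose, with the fourth card returned at Visit 6. Enter the checklist and card in Table 2 and in the visit lists of section 7.3.

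No extra visit or staff is needed, but the work is not nil:

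- Checklists: 24 × 4 × 2 = 192 around dosing, plus 24 at Visit 6, giving 216.
- Diary cards: 24 × 4 = 96, or 96 × 7 = 672 subject-days of short entries.

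All of it falls under the full source verification in section 10.1. More mild events will be reported, including some unrelated to the vaccine, which the baseline checklist and the Endocine-only arm help to interpret.
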